# Cognitive Training for Emotion-Related Impulsivity and Rumination: Protocol for a Pilot Randomized Waitlist-Controlled Trial

**DOI:** 10.2196/54221

**Published:** 2025-02-19

**Keywords:** cognitive control, cognitive training, emotion regulation, emotional response inhibition, emotional working memory, executive function, impulsivity, rumination, transdiagnostic, urgency

## Abstract

**Background:**

Inhibitory deficits are common in psychopathology. Emotion-related impulsivity (ERI) and rumination are general risk factors for psychiatric distress that are similarly associated with dysfunctional inhibition—particularly in affective contexts. A number of cognitive remediation procedures have been developed to improve inhibitory control; however, most remediation programs focus on “cold” cognition independent of affective processing. This pilot trial will gather preliminary evidence for a new cognitive training intervention targeting “hot” affective control (ie, inhibitory functions during elevated emotional arousal) in a transdiagnostic sample of adults who report heightened emotion dysregulation.

**Objective:**

This manuscript describes a protocol for a pilot randomized waitlist-controlled trial to assess changes in ERI and rumination after neurobehavioral affective control training (N-ACT), an 8-week cognitive training intervention designed to improve emotional response inhibition and emotional working memory. Our primary aim is to evaluate the efficacy, feasibility, and acceptability of N-ACT in reducing rumination and ERI, which we respectively conceptualize as complementary cognitive and behavioral consequences of emotion dysregulation. Secondarily, we will examine whether N-ACT leads to improvements in inhibitory control and, more distally, psychopathology symptoms.

**Methods:**

The final sample will comprise 80 adults who report high ERI or rumination. Participants will be randomized to (1) begin the N-ACT program without delay or (2) join a waitlist condition and then complete N-ACT. Exclusion criteria include active alcohol or substance use disorders, psychosis, and suicide risk. At the baseline and postintervention time points, participants will complete measures of emotion dysregulation and psychiatric symptoms, as well as a neuropsychological assessment of inhibitory control. Individuals assigned to the control group will undergo an identical assessment before joining the waitlist, followed by parallel assessments before and after N-ACT.

**Results:**

This trial is funded by support from the University of California Board of Regents and the Peder Sather Foundation (funding period: October 2022-September 2025). Recruitment is scheduled to begin in spring 2025. We will begin data analysis once data collection is complete, which is planned to occur in fall 2025.

**Conclusions:**

This pilot randomized waitlist-controlled trial is designed to assess the initial efficacy, feasibility, and acceptability of N-ACT, a novel cognitive remediation approach developed to address 2 key contributors to psychopathology: ERI and rumination. The N-ACT program uses computerized adaptive behavioral tasks to strengthen the affective control processes theoretically and empirically linked to ERI and rumination. We hope this work will help inform future studies with sufficient statistical power to ascertain whether enhancing affective control through cognitive training (N-ACT) produces downstream reductions in psychiatric symptoms via improved emotion regulation.

**Trial Registration:**

ClinicalTrials.gov NCT06226467; https://www.clinicaltrials.gov/study/NCT06226467; Open Science Framework Registry rak5z; https://osf.io/rak5z

**International Registered Report Identifier (IRRID):**

PRR1-10.2196/54221

## Introduction

### Background

Emotion dysregulation is an established risk factor for nearly all psychiatric syndromes, with particularly strong effects for anxiety and depression—the 2 most common psychological disorders [1,2].These links between emotion dysregulation and psychiatric dysfunction are well documented across ecological and laboratory studies, as well as in large-scale prospective work [3-5]. This research will evaluate a novel intervention, neurobehavioral affective control training (N-ACT), which is designed to target two trait-like facets of emotion dysregulation: (1) *rumination*, the tendency toward self-focused, past-oriented, repetitive negative thinking about the causes and consequences of negative affect [6,7]; and (2) *emotion-related impulsivity* (ERI; [8]), the tendency toward reduced behavioral control during states of high affective arousal [9], most commonly captured using measures of Urgency. These 2 aspects of emotional dysregulation reflect cognitive and behavioral responses, respectively, to negative affect. Robust associations have been documented of rumination and ERI with anxiety and depressive disorders as well as numerous other psychiatric conditions [6,7,10-18].

### Inhibitory Control Deficits in Psychopathology

Rumination and ERI are both tied to problems with cognitive (inhibitory) control. Cognitive control is a multifaceted construct that includes (1) the ability to update and manipulate the contents of working memory; and (2) the inhibition of task-inappropriate behavior (ie, response inhibition), alongside closely related executive functions (eg, cognitive inhibition, set shifting or task switching). This project targets both working memory and response inhibition, which represent promising candidate mechanisms linking emotion regulation deficits to varied manifestations of psychopathology.

Cognitive difficulties associated with major depressive disorder (MDD) and other internalizing syndromes often have severe consequences for the individuals affected, likely through adverse influences on symptoms and role functioning. Systematic reviews of this literature suggest that cognitive control deficits in MDD are not simply epiphenomenal effects caused by symptoms—as some have recently suggested [19]—but rather often persist after remission, thereby exerting continued influence on everyday functioning and the likelihood of symptom recurrence [20,21]. Indeed, impaired cognitive control predicts relapse in patients with first-episode depression [22] up to 5 years after the index episode through its association with rumination [23,24]. One of the longest prospective studies of cognition in MDD revealed cognitive control impairment a full decade after symptom remission [25]. In sum, a substantial literature implicates poor cognitive control in prolonged vulnerability to depression recurrence and relapse.

Evidence for chronic neuropsychological deficits in MDD and other psychiatric disorders has generated interest in improving mental health through strengthening cognitive control and other executive functions. However, traditional psychotherapeutic interventions have limited effects on cognitive control; for example, meta-analyses indicate little to modest changes in cognitive control capacities after psychological [26] or pharmacological treatment for depression [27]. The recognition of the need for new approaches to enhancing executive functions has led to a growing focus on development of cognitive remediation or training programs that directly target inhibitory control [28-30].

However, many studies—of major depression or otherwise—rely on measures of “cold” cognitive control, in that the assessment procedures lack emotionally salient stimuli or probes. *Affective control* refers to the ability to exert inhibitory control in situations or tasks involving emotionally arousing content, often referred to as “hot” executive functions. Emotional contexts may be more likely to activate or aggravate symptoms compared to contexts without such affective components [31]. Rumination and ERI—as well as psychopathology more broadly—may be more closely linked to affective control deficits than to cold cognitive control deficits. For example, among people with remitted MDD compared to healthy controls, Ronold et al [32] observed working memory deficits (during high cognitive load) especially for negative compared to positive emotional content; moreover, in 2 independent samples, such impairment was tied to heightened rumination [33], which in turn predicted elevated risk for depressive relapse [32]. ERI is similarly associated with impaired inhibitory control, particularly during higher arousal states [34]. Moreover, poor affective control is associated with symptoms of eating disorders [35], nonsuicidal self-injury [36-40], and suicidal behaviors [31,41,42]. Thus, affective control is an empirically justified and theoretically informed target to remediate and prevent the recurrence of psychiatric symptoms.

A growing corpus of research has converged on 2 components of affective control, both of which are targeted by N-ACT: (1) *emotional working memory*, which involves the temporary storage and manipulation of emotional information in short-term memory; and (2) *emotional response inhibition*, or the ability to regulate motor impulses driven by automatic emotional reactions. Dysfunction in working memory or response inhibition—*specifically in the context of negative emotion*—is independently tied to rumination, ERI, and internalizing symptoms, as well as self-injurious thoughts and behaviors [39,41,43-46]. Several studies have shown that emotional response inhibition, as indexed by an emotional stop-signal task (ESST), shows significant correlations with measures of ERI and psychiatric severity [37,39,43]. Negative emotional response inhibition impairment is a strong predictor of symptoms, including increased risk of future suicide attempts [41].

### Cognitive Remediation in Psychiatry

The goal of cognitive remediation is to improve dysfunctional neurocognitive processes. This improvement relies on the repeated practice of specialized cognitive training exercises using computer algorithms that adjust task difficulty according to user performance. A burgeoning literature suggests that cognitive remediation may be a promising transdiagnostic intervention approach [28,47-55]. Working memory training has been found to reduce the recurrence of mood episodes among patients with remitted MDD, with stronger protective effects—apparent up to 2 years after the intervention—for those who reported reduced rumination after training [52,56]. Although accumulating evidence supports the efficacy of cognitive remediation in psychiatric disorders, meta-analytic effect sizes tend to be small to medium [28], and a substantial proportion of individuals do not respond to existing training programs for symptom reduction [57].

Numerous issues likely contribute to the relatively modest treatment effects associated with standard cognitive remediation programs. N-ACT is novel in 3 ways. First, we focus on emotion regulation rather than psychiatric symptoms as our primary outcome. Second, extant literature shows considerable variability in the delivery methods of cognitive remediation. Following consensus recommendations from an expert working group [47], we will implement scaffolding techniques to facilitate the generalization and functional impacts of N-ACT. More specifically, we will follow recommendations to provide support to facilitate translation of skills into everyday activities, so as to enhance the ecological validity and effectiveness of cognitive training programs [47-55]. Participants will accordingly complete N-ACT intervention sessions guided by a “coach,” who will deliver semistructured and (partially) personalized psychoeducational content. N-ACT coaching sessions will include the identification of compensatory problem-solving strategies for emotion regulation, skills practice, motivational enhancement, discussion of the ecological relevance of the cognitive skills being trained, and procedures to promote the transfer of training effects to real-world situations. Therefore, we will be testing the effects of repeated affective control exercises, coupled with therapeutic coaching. Our hope is that this combination of techniques will support generalization to improved functional outcomes.

Third, although the stimuli and parameters in many cognitive control training tasks (eg, those using geometric shapes and letters) lack inherent salience value, our trial builds from a smaller body of work on cognitive remediation using the affective variants of inhibitory control tasks as well as traditional tasks (with neutral stimuli) that may naturally induce emotional arousal [50]. As an example of the latter, the Paced Auditory Serial Addition Test [58], which uses numerical stimuli and has been extensively implemented as an adaptive training task [29,30,59], characteristically evokes frustration [58]. To our knowledge, the only direct comparison of cold versus hot cognitive remediation was performed in a pilot trial of emotional working memory training, which yielded promising results in symptoms and cognition (but not rumination) among patients with depressive symptoms [60]. This early work is consistent with recent meta-analytic findings suggesting that hot inhibitory control training may be more effective than nonaffective cognitive remediation procedures for psychopathology [61]. Accordingly, N-ACT incorporates affective stimuli (eg, naturalistic images with standardized emotional content) into traditional training tasks designed to improve cognition such that users learn to use these mental operations in socioemotional contexts that more closely match in vivo experiences. The inclusion of affective stimuli is particularly important, given a substantial body of work suggesting that difficulties sustaining inhibitory control during states of elevated arousal are particularly relevant to emotion regulation and psychiatric symptoms.

### This Study

#### Overview

This pilot randomized waitlist-controlled trial will enroll adult participants with high rumination or ERI scores. The primary aim of this study is to examine the acceptability, feasibility, and efficacy of N-ACT as a novel therapeutic approach to reduce rumination and ERI by improving 2 facets of affective control: emotional working memory and emotional response inhibition. Secondarily, we will test the effects of N-ACT on behavioral indices of ability transfer as well as on other subjective measures of emotion dysregulation (beyond trait rumination and ERI) and psychopathology symptom severity (refer to Multimedia Appendix 1 for details). Finally, we will conduct exploratory analyses to examine the potential mechanisms that might influence predicted changes in emotion dysregulation, informing future work to systematically test these effects in a sufficiently powered sample. In addition to performing intent-to-treat analyses, we will conduct sensitivity analyses to evaluate the extent to which program adherence predicts the hypothesized effects.

#### Hypotheses

We propose the following hypotheses:

H1: Participants will rate N-ACT as an acceptable intervention to reduce emotion dysregulation.H2: Participants will demonstrate adherence to the N-ACT program at levels comparable to those observed in established cognitive remediation protocols [33,52,62-64].H3 (primary): Compared to baseline, participants assigned to complete N-ACT (without a waitlist) will report greater decreases in rumination and ERI at the postintervention assessment than those assigned to the control condition at the postwaitlist assessment.H4 (secondary): Compared to baseline, participants assigned to complete N-ACT (without a waitlist) will demonstrate greater improvements in targeted affective control processes (ie, enhanced emotional working memory and emotional response inhibition) at the postintervention assessment than those assigned to the control condition at the postwaitlist assessment.H5 (secondary): Compared to baseline, participants assigned to complete N-ACT (without a waitlist) will demonstrate near (ie, enhanced hot affective flexibility) and far (ie, enhanced cold working memory and cold response inhibition) transfer of trained neurocognitive abilities at the postintervention assessment than those assigned to the control condition at the postwaitlist assessment.H6 (secondary): Compared to baseline, participants assigned to complete N-ACT (without a waitlist) will report greater decreases in self-rated psychopathology symptom severity (ie, reduced internalizing and externalizing symptoms) at the postintervention assessment than those assigned to the control condition at the postwaitlist assessment.

## Methods

### Overview

This research comprises a delayed intervention randomized waitlist-controlled trial with a mixed, 2-group (2 between-subject levels: active vs control), repeated measures (2 within-subject levels: T1=baseline or preintervention time point; T2=postwaitlist or postintervention time point) design, for which we will recruit English-speaking adults (aged 18-65 y) from the San Francisco Bay area of the United States. The inclusion criteria include high self-reported rumination or ERI. Eligible individuals will be invited to the university for an initial baseline session. At this session, they will complete informed consent procedures and an assessment battery consisting of computerized neuropsychological tasks with concurrent psychophysiological monitoring. After the baseline session, participants will complete a battery of questionnaires, followed by 1 week of baseline ecological momentary assessment (EMA) of real-world daily fluctuations in mood, rumination, and ERI.

After the baseline assessment (laboratory session, questionnaires, and EMA), we will randomly assign participants to receive active treatment (ie, N-ACT without delay) or the waitlist control condition, unblinded, using an asymptotic maximal procedure to achieve a maximally tolerated imbalance of 2, while maintaining a 1:1 allocation ratio between the 2 trial arms [63]. Participants in the active N-ACT group will begin the intervention, which consists of 8 weekly coached training sessions, within 1 week after baseline EMA. We will recontact waitlist control participants after a period equivalent to the intervention duration (ie, 2 months) to complete a second (postwaitlist) assessment session and EMA before starting the N-ACT program for the following 8 weeks. After the intervention, participants will be asked to complete a second week of EMA, and then a postintervention assessment session with comparable measures to baseline. We will recontact waitlist control participants approximately 10 weeks after their (prewaitlist) baseline assessment session to complete a second (postwaitlist) assessment and 1 week of EMA, parallel with the pre-intervention assessment procedures of the N-ACT group,. The waitlist group will then be offered 8 weeks of N-ACT, followed by a second week of postintervention EMA, and then a final assessment session. In sum, we will follow participants assigned to receive the intervention without delay for 12 weeks (3 mo) and those assigned to the waitlist control group for 22 weeks (5.5 mo). This delayed intervention randomized waitlist-controlled trial design enables us to offer all interested participants the opportunity to participate in the program and maximizes our ability to rapidly accrue a sufficiently sized sample for analyses. Figure 1 demonstrates the flow of potential participants through the study procedures.

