### Ethical Considerations

The University of California Berkeley Committee for Protection of Human Subjects granted approval for this research (2023-01-15949) before data collection. All participants will complete written informed consent before commencing study procedures.

Participants will be assigned an ID number, which will be used in place of their name or other identifying information on all research materials. Data will be kept in secure, password-protected files. Although we plan to make data publicly available for reanalysis, we will carefully deidentify data before doing so. In publishing or presenting the results, we will not provide any information that could identify an individual participant.

Participants will receive course credit or monetary compensation for completing assessment procedures but will not be paid for time spent on screening or the intervention itself. Students will be able to earn credit toward required research hours in their psychology classes. We plan to increase the hourly payment rate slightly over the course of the trial to promote retention, from US $20/h for the baseline assessment to US $30/h for the postwaitlist and postintervention assessments. We will compensate participants up to US $60 (or 3 h of course credit) for completing the baseline assessment (2.5-h in-person session plus 30 min of questionnaires), a US $10 “bonus” for performance on an unrelated computer task during the baseline session, US $10 for each week of EMA if they complete at least 75% of the prompts, and US $60 for the postintervention assessment (1.5-h in-person session plus 30 min of questionnaires). Those randomized to the waitlist control condition will be eligible to receive up to an additional US $60 for completing the postwaitlist assessment (identical to the postintervention assessment).

In sum, participants assigned to complete N-ACT without the waitlist can earn up to US $150 (or 3 h of course credit plus up to US $90), while those in the waitlist control condition could earn up to US $70 in addition to those amounts. Payments will be prorated if participants complete only part of an assessment. We will remunerate participants within 1 week of each completed assessment via digital credit cards, which will be replenished as necessary.

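### At T2 the N-ACT arm completes its EMA week before the session and primary questionnaires and the waitlist arm after them, so a recent week of self-monitoring is aligned with treatment

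*Protocol article*

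**What the plan says.** All references are to the Protocol article.

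- **Baseline, both arms (Methods, Overview).** The laboratory session comes first, then the questionnaires, "followed by 1 week of baseline ecological momentary assessment (EMA".
- **N-ACT arm (Methods, Overview).** Training starts "within 1 week after baseline EMA" and consists of "8 weekly coached training sessions". After that, "participants will be asked to complete a second week of EMA, and then a postintervention assessment session". The total is given as: "we will follow participants assigned to receive the intervention without delay for 12 weeks (3 mo").
- **Waitlist arm (Methods, Overview).** Recontact is described twice. The first time it is "after a period equivalent to the intervention duration (ie, 2 months"), for an assessment session and EMA. The second time: "We will recontact waitlist control participants approximately 10 weeks after their (prewaitlist) baseline assessment session to complete a second (postwaitlist) assessment", and then a week of EMA, stated to parallel the N-ACT group's pre-intervention procedures. Total follow-up is 22 weeks.
- **Questionnaires (Assessment, Overview; Questionnaires).** They follow each in-person session, within 24 hours.
- **EMA content (EMA Surveys).** There are five prompts a day, covering negative mood, rumination and impulsivity.
- **Primary analysis (Statistical Analysis Plan).** T2 is the postintervention assessment in N-ACT and the postwaitlist assessment in the control arm. The group×time interaction on RRS-B and TFII-FTA is the index of treatment effect.

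**The concern.** The primary comparison treats the two T2 assessments as equivalent points on the same path, one with N-ACT and one without. At T1 both arms answer before any EMA. At T2 only the N-ACT arm answers straight after a new week of repeated questions about the two constructs that form the primary outcomes. A pattern that is absent at T1 and present in one arm at T2 has the same form as a group×time interaction. If a week of self-monitoring shifts RRS-B or FTA in either direction, the shift is counted as part of the N-ACT effect. It coincides with arm for everyone who follows the schedule, so neither a covariate nor a sensitivity analysis can separate it. A waitlist design does not require this asymmetry.

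**Working it through.** **1. Order.** The two sequences around T2, side by side:

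| Arm | First | Second | Third |
|---|---|---|---|
| N-ACT | EMA week | session | questionnaires (within 24 h) |
| Waitlist | session | questionnaires (within 24 h) | EMA week |

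The N-ACT order is explicit. The waitlist order is read from three things that agree: both descriptions list the assessment before EMA, the second likens the visit to the pre-intervention procedures, and those run session, questionnaires, EMA.

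**2. EMA exposure before the T2 questionnaires.** One week is 5 × 7 = 35 scheduled prompts.

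- N-ACT: baseline week + second week = 2 weeks = 70 prompts, the last 35 immediately before T2.
- Waitlist: baseline week only = 1 week = 35 prompts, about two months earlier.

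The payment figures in Ethical Considerations confirm the number of EMA weeks. N-ACT: 60 + 10 (task bonus) + 2 × 10 (EMA) + 60 = US $150, as stated. Waitlist extra: 60 + 10 (one more EMA week) = US $70, as stated.

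**3. Timing of T2, in weeks from the baseline session.**

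- The stated waitlist total reproduces: 10 to T2 + one 12-week N-ACT block = 22.
- N-ACT from its components: 1 (EMA) + 0 to 1 (start) + 7 to 8 (eight weekly sessions, first to last or nominal) + 1 (EMA) = week 9 to 11. The stated 12 needs about one further week for the final session and questionnaires.
- Waitlist: about week 10. If the 2 months run from the end of baseline EMA, 1 + 8 to 8.7 = week 9 to 9.7. If they run from the latest training start, 2 + 8 = week 10.
- Gap (N-ACT minus waitlist at week 10): 9 − 10 = −1 to 12 − 10 = +2 weeks, which includes zero.

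**4. What a shift would do (assumption).** The document gives no size for a self-monitoring effect, so a range is assumed. Take one outcome, 40 per arm, no true effect, a change-score comparison with a normal approximation, and T1–T2 correlation ρ. The standard error in SD units is √(2(1 − ρ)) × √(2/40), which is 0.224 at ρ = 0.5 and 0.173 at ρ = 0.7. With a spurious shift b, the two-sided 5% test rejects with probability 1 − Φ(1.96 − b/SE) + Φ(−1.96 − b/SE):

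| Assumed b (SD) | ρ = 0.5 | ρ = 0.7 |
|---|---|---|
| 0 | 5.0% | 5.0% |
| 0.05 | 5.6% | 6.0% |
| 0.10 | 7.3% | 8.9% |
| 0.20 | 14.5% | 21.1% |

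For scale, 0.05/0.35 = 14% of the planned effect size. The table shows sensitivity only and does not estimate the bias.

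**The case against.** The strongest reply is that the effect on these outcomes is speculative. RRS-B is described as measuring a disposition and the TFII as trait-like, so neither is a momentary score. Both arms have already had an EMA week. Prompts about rumination could as well raise scores and work against N-ACT. A small shift of 0.05 SD barely moves the false-positive rate. In an unblinded waitlist pilot, expectancy and attention probably matter more. All of this stands as a limit on size and direction. It does not remove the asymmetry, and unlike those larger problems this one is avoidable.

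A second reply is that the article is condensed, that Figure 1 is not shown, and that the waitlist order is partly inferred. Exact visit windows may well be left to the full protocol. The order, however, is in the printed schedule, and both descriptions of the waitlist visit agree on it.

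A reader might also infer several stronger points that the document does not support:

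- **Contradictory waitlist intervals.** The 2 months and the 10 weeks can be reconciled. The first can be counted from after baseline EMA, while the second is counted from the baseline session.
- **A T1–T2 interval 20% longer in N-ACT (12 weeks against 10).** The 12 weeks is total follow-up, not a scheduled T2 date, and the components reach 11 at most.
- **A conflict with Ethical Considerations.** The phrase "completing the postwaitlist assessment (identical to the postintervention assessment") stands in a payment paragraph and concerns content and duration. The instruments are indeed the same.
- **35 prompts against none.** This is true only of the week just before T2. The overall contrast is two weeks against one.
- **A bias in favour of N-ACT.** Nothing in the document fixes the direction.

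**Conclusion.** The point holds for order. As written, the T2 session and the primary self-reports follow a fresh EMA week in N-ACT and precede it on the waitlist: 70 against 35 scheduled prompts before T2, with the extra 35 immediately before it. The difference is aligned with arm and falls on the group×time interaction. This rests on reading the waitlist T2 in the pre-intervention order, as the text says. The size and direction of any bias are unknown.

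The timing part is weaker. T2 is loosely matched between arms, with a gap of −1 to +2 weeks that may be zero. This calls for clarification and does not establish a confound. The whole is a cheap change worth making before recruitment, not a fault that invalidates the trial.

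**What to change.** In Methods, Overview:

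1. Use the same order of session, questionnaires and EMA at T2 in both arms. Session and questionnaires first, then EMA, would match baseline. Applied also to the waitlist arm's final assessment, it would keep the same order at T1 and T2 in the supplementary pre-post models that pool everyone who completes N-ACT. EMA first in both arms would also remove the difference between arms.
2. Set one T2 target week and window for both arms, counted from a common origin (baseline session or randomisation), and restate the 2 months, 10 weeks and 12 weeks on that origin. If the N-ACT session moves ahead of its EMA week, the components put it at 1 + 0 to 1 + 7 to 8 = week 8 to 10, so the common target should be set with the new order in view.

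Ethical Considerations needs no correction. The cost is protocol wording and the rescheduling of one EMA week, with no extra visits or data. The article states that recruitment had yet to begin.
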